# RISEinFAMILY project: the integration of families at neonatal intensive care units (NICUs) to empower them as primary caregivers: study protocol for a stepped wedge cluster controlled trial

**DOI:** 10.1186/s13063-024-08043-7

**Published:** 2024-04-10

**Keywords:** Family integrated care, Parent empowerment, Family-centred rounds, Neonates, Stress, Stepped wedge cluster controlled trial

## Abstract

**Background:**

Family Integrated Care (FICare) has demonstrated positive outcomes for sick neonates and has alleviated the psychological burden faced by families. FICare involves structured training for professionals and caregivers along with the provision of resources to offer physical and psychological support to parents. However, FICare implementation has been primarily limited to developed countries. It remains crucial to assess the scalability of this model in overcoming social-cultural barriers and conduct a cost-effectiveness analysis. The RISEinFAMILY project aims to develop an adapted FICare model that can serve as the international standard for neonatal care, accommodating various cultural, architectural, and socio-economic contexts.

**Methods:**

RISEinFAMILY is a pluri-cultural, stepped wedge cluster controlled trial conducted in Spain, Netherlands, the UK, Romania, Turkey, and Zambia. Eligible participants include infant-family dyads admitted to the Neonatal Intensive Care Unit (NICU) requiring specialised neonatal care for a minimum expected duration of 7 days, provided there are no comprehension barriers. Notably, this study will incorporate a value of implementation analysis on FICare, which can inform policy decisions regarding investment in implementation activities, even in situations with diverse data.

**Discussion:**

This study aims to evaluate the scalability and adaptation of FICare across a broader range of geographical and sociocultural contexts and address its sustainability. Furthermore, it seeks to compare the RISEinFAMILY model with standard care, examining differences in short-term newborn outcomes, family mental health, and professional satisfaction.

**Trial registration:**

ClinicalTrials.gov NCT06087666. Registered on 17 October 2023. Protocol version: 19 December 2022; version 2.2.

**Supplementary Information:**

The online version contains supplementary material available at 10.1186/s13063-024-08043-7.

## Introduction

### Background and rationale {6a}

Family Integrated Care (FICare) promotes the active participation of family members in providing specialised care to their sick newborn baby admitted to the neonatal intensive care unit (NICU). This change in paradigm in neonatal care, initially developed and implemented at Mount Sinai Hospital in Toronto in the stable preterm infant, has shown promising results in improving health outcomes in this population. The first pilot study conducted by O’Brien et al. demonstrated that parental involvement in direct care led to better weight gain, increased breastfeeding rates, and reduced stress and anxiety levels among parents of preterm infants [1].

These findings were further supported in a cluster-randomised controlled trial [2], as well as in subsequent studies highlighting the positive effects of the model in accelerating maturation processes [3] (earlier full enteral nutrition [3, 4]) shorter duration of mechanical ventilation and hospital length of stay [5–9], decreased rates of late-onset sepsis [5, 6], and improvements in neurobehaviour at 18 months [7]. Recently, Moreno-Sanz [8] described the successful adaptation and implementation of FICare policies also in the unstable, critically ill premature infant and the high-risk neonate with complex medical or surgical conditions, suggesting the potential for generalising the FICare model as the standard of care in NICUs.

However, the FICare model has only been tested up to now in high-income, developed countries. FICare relies on structured professional and caregiver training and parental physical and psychological support, which implies the provision of resources. Yet, the scalability of the model to overcome social-cultural barriers and cost-effectiveness analysis has not been tested.

RISEinFAMILY is an international consortium that has been designed for adapting and implementing FICare in different regions of Europe and Africa. The expansion of FICare to other NICUs and countries necessitates further research to identify potential constraints that may limit its adoption, particularly in low- and middle-income countries with different sociocultural contexts. Understanding these barriers and developing strategies to address them will be crucial in realising the full potential of FICare and ensuring its successful implementation globally.

### Objectives {7}

The aim of the RISEinFAMILY project is to develop a FICare model adapted to different cultural, architectural and socio-economic contexts as the new international standard for neonatal care and provide sound data on its sustainability based on a cost-effectiveness analysis.

The adapted FiCare model (herein after RISEinFAMILY model) will include a wider geographical and sociocultural diversity and 2 implementation levels (basic and advanced) and will try to demonstrate its superiority, against routine current provision of care, in infants’ clinical outcomes, parental mental health and professional’s self-care and satisfaction.

### Trial design {8}

This quality improvement project is designed as an international, multi-centre, pluri-cultural prospective stepped-wedge cluster controlled trial. Five non-FICare-experienced NICUs from Netherlands, Turkey, Romania, the UK and Zambia (sites 1–5) and two clinical sites who have recently implemented FICare from Spain and Netherlands (sites 6 and 7) are expected to be recruiting infants into this trial that will include at least 552 babies during a 32-month period (see Fig. 1). The stepped wedge cluster design was selected due to the nature of the intervention, which involves changes to unit-level provision of care and interaction between participants, with a risk of cross-contamination.

**Fig. 1 Fig1:**

Schematic illustration of stepped wedge cluster trial

## Methods: participants, interventions and outcomes

### Study setting {9}

Six academic hospitals from Netherlands, Turkey, Romania, the UK, Zambia and Spain (sites 1–6) and one non-academic hospital (site 7) will collect data for this study. The list of the study sites of the RISEinFAMILY consortium, H2020-MSCA-RISE-2020, can be found here https://cordis.europa.eu/project/id/101007922 [9].

### Eligibility criteria {10}

We will include infants born with birth weight at or below 1500 g or gestational age at or below 34 weeks, any other peri-neonatal condition anticipating NICU specialised care with an admission for at least 7 days and the decision to provide full life support. Further, we will include parents if they are willing to spend at least 6 h per day at NICU or committed to attending educational sessions, an active involvement in care of their infant for at least a 7-day period, not to have an intellectual or language barriers to understanding, at least one primary caregiver is involved in the training and signed informed consent. We will exclude infants with the decision not to provide full life support, critical illness unlikely to survive or scheduled for early transfer to another non-FICare hospital. We will exclude parents if they have an intellectual handicap that makes learning-understanding difficult, communication cannot be established even with a translator, have mental psychiatric problems or under legal supervision, or guardianship of social services, and finally, lack of parental signed informed consent.

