### Interventions

#### Explanation for the choice of comparators {6b}

A cohort of patients, born at clinical sites 1 to 5 from the beginning of the study to the time assigned to start the intervention, will be assigned to the control group, representing standard neonatal care.

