#### Intervention description {11a}

The study will start at the same time at all participating sites that will continue to provide routine clinical care according to their current policies. Prospective data gathering will be accomplished.

A start point for the experimental intervention (3, 6, 9, or 12 months from the start of the study) will be assigned for each clinical site (1 to 5) taking into account the expected time internally needed to overcome all logistics and regulatory issues with a potential impact on FICare implementation. A 3-month wash-out period will be used for the local training process and assessment of site readiness, while enrolment will be halted. After that, recruiting will continue, and the experimental intervention will be started. Clinical sites 6 and 7 will run the experimental intervention from the start of the study, without pauses.

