##### Training and certification

The RISEinFAMILY training programme is divided into two curricula: for healthcare professionals/staff (Training the trainers) and for families (Education of caregivers), the latter being categorised into two intervention levels (basic and advanced). The following modules are identified as the minimum training contents to be delivered to foster RISEinFAMILY:*Training the trainers:* (1) understanding the boundaries of the FICare model; how to promote FICare among families; (2) psychosocial needs of families (resilience, stress and anxiety, or mourning); communication skills (assertive communication); (3) how to involve families in NICU (safe conduct in NICU environment, attachment and bonding, how to do family-centred medical rounds); (4) professional self-care (burnout, compassion fatigue).*Education of caregivers:* (1) comprehensive description of the FICare model (the strengths and training methodology) and the functional and architectural structure of the NICU; (2) family self-care (stress and anxiety, resilience, or mourning); (3) learning about infants’ neurobehavior, stress and pain; (4) taking part in baby care (basic level), where parents will be “professionalised” as to become the first line care provider of their children; (5) taking part in baby care (advanced level), specific task’s training for infants who require even more specialist care; (6) parents will be prepared for home; a map of the social resources available at the local setting will be provided.

A teacher education system will be used for staff training. Mentor-assigned trainee groups and the calendar for meetings will be defined by site co-ordinators. The procedure will include face-to-face meetings, e-learning tools or a combination of methods adapted to centre facilities and organisational features, in order to accomplish the programme and procedures dissemination among 90% of the NICU staff.

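### Being involved in the caregiver training is an entry criterion for the whole trial, yet that training belongs to the intervention, so the clause cannot be applied alike in both phases

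*Protocol article*

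**What the plan says.** Eligibility criteria {10} gives one list of parent criteria for the whole trial. Parents must be "willing to spend at least 6 h per day at NICU or committed to attending educational sessions", must undertake "an active involvement in care of their infant for at least a 7-day period", must have no intellectual or language barrier, and must meet the item at issue: "at least one primary caregiver is involved in the training and signed informed consent". No item is marked as applying to one phase only.

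Under Explanation for the choice of comparators {6b}, infants born at sites 1–5 before their site's start point "will be assigned to the control group, representing standard neonatal care". Intervention description {11a} says that all sites at first "continue to provide routine clinical care according to their current policies". It then adds: "A 3-month wash-out period will be used for the local training process and assessment of site readiness, while enrolment will be halted".

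Training and certification describes the training as part of the model: "The RISEinFAMILY training programme is divided into two curricula", one for staff and one for families.

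**The concern.** An entry criterion that only an intervention family can satisfy does not define one population for a before-and-after comparison. Statistical methods {20a} takes the effect of the intervention from control versus intervention data at the non-experienced centres. Order of crossover is not randomised (Sequence generation {16a}), and hospitals and staff are not blinded (Who will be blinded {17a}). Comparability therefore depends heavily on the same kind of family entering in each phase.

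If families are screened on real involvement in training after crossover and not before it, the intervention phase may hold families who differ in engagement. Engagement could plausibly bear on kangaroo care, infant growth and the parent questionnaires, so part of any observed difference could come from who was enrolled rather than from the model of care.

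**Working it through.** This is mainly a check of the text. The arithmetic at the end only shows scale.

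**Step 1. Can a control family meet the clause?** The family curriculum is part of the RISEinFAMILY programme. Control-phase units follow current policies. Local training takes place in the wash-out, after the control phase and with enrolment stopped. So no control family has a trial training to be involved in. Read literally, the number of eligible control families is zero, which contradicts the comparator section.

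**Step 2. How could sites apply it?**

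| Use of the clause | Before crossover | After crossover | Same selection? |
|---|---|---|---|
| Literal | nobody qualifies | involved families | no control group |
| Waived for controls | not applied | applied for real | no |
| Hypothetical for controls | would take part if offered | does take part | not necessarily |
| Willingness only, both phases | would take part | would take part | yes, but not what is written |

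The article does not say which was used.

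**Step 3. What is shared by both phases?** Six hours of presence satisfies the first item in either phase, because commitment to sessions is only an alternative to it. Seven days of active involvement and consent also apply throughout. The difference is therefore confined to families who pass all of these and fail only the training clause. Call that fraction f.

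**Step 4. Does the analysis deal with it?** The model forces in gestational age and study site. Site adjustment cannot remove a difference between phases within a site. Further covariates come from backward selection at p < 0.1 among unnamed potential confounders. Parental variables might be kept, but nothing ensures it.

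**Step 5. The plan's own figure.** Inputs from Sample size {14}: difference 1.9 g/kg/d, SD 2.5, α = 0.05 (taken as two-sided), power 95%.

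n = 2 × (1.960 + 1.645)² × (2.5/1.9)² = 2 × 12.995 × 1.731 ≈ 45 per group. The t-test version gives 45.98, so 46, as stated. The clause changes no stated figure.

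**Step 6. Scale, on assumed values only.** If fraction f is left out in the intervention phase alone, and those infants gain g less, the spurious difference is b = f × g. With f = 0 it is 0. With g = 1 g/kg/d and f = 0.2 to 0.4 it is 0.2 to 0.4 g/kg/d, and 0.2/1.9 = 11% to 0.4/1.9 = 21% of the target. Neither f nor g is in the document, and the shared conditions of step 3 may make f small.

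With no true effect, SE = 2.5 × √(2/n), and the two-sided rejection rate is 1 − Φ(1.96 − b/SE) + Φ(−1.96 − b/SE):

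| Assumed b (g/kg/d) | 46 per group (SE 0.521) | 276 per group (SE 0.213) |
|---|---|---|
| 0 | 5.0% | 5.0% |
| 0.1 | 5.4% | 7.6% |
| 0.2 | 6.7% | 15.6% |
| 0.3 | 8.9% | 29.1% |
| 0.5 | 16.0% | 65.2% |

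The second column halves the planned 552 babies. That ignores clustering and counts sites 6 and 7, which contribute no controls, so it is an upper illustration. The rates are the same for a shift in either direction. A larger sample does not reduce this bias; it makes a false finding more likely.

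**The case against.** Several points on the other side stand.

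- A reader might infer that commitment to training is compulsory. It is not: sessions are joined by an *or* to six hours of presence. Only the separate involvement clause is tied to the intervention.
- A reader might infer that controls are unselected for time and motivation. They are not: presence or sessions, seven days of involvement and consent apply to them too, so the remaining difference is narrower.
- A reader might infer that the bias favours the intervention on growth, kangaroo time and every parent scale. Nothing in the article links involvement in training to these outcomes at baseline, so the direction is unknown.
- A reader might see the same fault in excluding infants "scheduled for early transfer to another non-FICare hospital". There, non-FICare describes the receiving hospital. That does not depend on the phase of the sending site, so the same transfers are excluded before and after crossover. The wording is at most awkward.
- Table 1 schedules parental data and questionnaires at enrolment, and further covariates may enter the model, so some adjustment for parental differences is possible.
- The article condenses a full protocol that is not shown and that may say how the clause was applied to controls.

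The last point softens the conclusion without removing it. This is not a missing detail: the criterion is printed, and as printed it conflicts with the comparator.

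**Conclusion.** The point holds in a limited form. The training clause either excludes every control family or has to be used differently by phase, in a non-randomised and unblinded comparison. Families may therefore differ by phase on engagement. The shared entry conditions reduce that risk, and the forced covariates do not address it.

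The size is unknown and could be nil, and the direction is unknown. The 11–21% of target and the inflated rejection rates show only what assumed shifts would do; they are not estimates for this trial. The verdict rests on two readings: that involvement means actual participation, as the wording suggests, and that no caregiver training was offered before crossover, as the intervention sections imply.

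**What to change.** **Wording.** Remove involvement in the training from eligibility, and treat training uptake as an intervention-phase implementation or adherence measure; completion of training is already among the implementation outcomes. Put one question to families in identical form in both phases: willing to be present six hours a day, or willing to attend educational sessions if offered. Keep both routes, since a presence-only question would shut out families who now qualify through the sessions.

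**Enrolment already done.** Enrolment began in February 2023, and start points lie 3 to 12 months after study start. If study start means that date at every site, control enrolment ended by about February 2024, before publication in April 2024. Rewording alone would then change only the intervention phase. So:

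1. State how the clause was applied to controls at each site, and align the remaining intervention-phase enrolment with that rule.
2. Report screened, eligible and consented counts by site and phase.
3. Compare by phase the parental data and questionnaires collected at enrolment.
4. Add a sensitivity analysis restricted to families who meet the common criterion, where the records allow, or adjusted for those baseline parental variables.

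**Cost.** An amendment to the eligibility text, retrieval of screening logs and one extra analysis. Some less engaged families will enter the intervention phase, which slightly dilutes the observed effect. Families already turned away cannot be recovered, so the counts in item 2 matter most.

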### Outcomes {12}

The study’s primary outcomes are as follows: (a) RISEinFAMILY implementation: proportion of families completing basic and advanced training levels (observed vs expected), average time to complete basic and advanced training levels (observed vs expected) and average time of kangaroo care per day (hours); (b) short-term health infant’s outcomes: proportion of high-risk infants achieving and maintaining adequate growth patterns during NICU admission, defined according to Patel’s method [10, 11].

The study’s secondary outcomes are as follows: reported adverse event rate per 1000 patients/day, feeding patterns and major morbidities at 36 weeks postmenstrual age (PMA) or discharge, nosocomial infection [12], necrotising enterocolitis (Bell’s > stage 2), moderate-severe brain injury (worst cranial ultrasound) [13], parental needs, empowerment and psychological health (stress [14], anxiety and depression [15, 16], self-efficacy [17], bonding [18], resilience [19]), professional’s self-care and satisfaction (anxiety and depression [15], burnout [20], post-traumatic stress [21], work and well-being [20]).

The study’s exploratory outcomes are as follows: economic impact (level of post-implementation utilisation of FICare, resources and costs associated with FICare implementation, cost-effectiveness estimates compared to the current care, expected value of current implementation and expected value of perfect implementation); mid-term infant’s general health (growth pattern during the first 12 months from birth, use of health system facilities after discharge); long-term neurodevelopment (survival without neurodevelopmental disabilities).

Specific items and test batteries are stated in Additional file 1.

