#### Questionnaires for parents

Abbreviated Parental Stressor Scale for Pediatric Intensive Care Unit (A-PSS:PICU) [22]: This scale, based on the PSS:PICU [14] includes 7 items to assess parental stress caused by the PICU environment. It has two factors (stress due to the child’s condition and stress related to PICU’s staff) and adequate internal consistency (*α* = 0.80). In this article, we have adapted the items to the NICU context.

Generalized Anxiety Disorder (GAD-7) questionnaire [23]: This is a seven-item questionnaire designed to assess the patient’s anxiety symptoms during the previous 2 weeks. It showed excellent internal consistency (*α* = 0.92) and test–retest reliability (intraclass correlation = 0.83). At a cut point of 10 showed the greatest sensitivity and specificity.

Edinburgh Postnatal Depression Scale (EDPS) [24]: This is a 10-item scale to measure depressive symptoms during the perinatal period. It showed excellent internal consistency (*α* = 0.91) and test–retest reliability (Spearman’s rho rank correlation = 0.90). The cutoff score of ≥ 13 indicates an elevated risk of depression.

The Perceived Maternal Parenting Self-Efficacy (PMP S-E) [17]: This is a 20-item questionnaire to measure maternal parenting self-efficacy, especially of hospitalised preterm neonates. It showed excellent internal consistency (*α* = 0.91) and test–retest reliability (Spearman’s rho rank correlation = 0.96).

The Postpartum Bonding Questionnaire (PBQ) [18]: It comprises 25 items with a 5-point Likert-type response scale. It measures the presence of bonding difficulties and has four subscales: affected bonding, rejection and hatred, anxiety about baby care, and risk of abuse. It provides a total score of the quality of bonding. It showed excellent internal consistency (*α* = 0.90) and test–retest reliability for the total scale (Spearman’s rho rank correlation = 0.96), and its subscales (Spearman’s rho rank correlation ranging from 0.77 to 0.95).

Brief Resilience Scale (BRS) [25] is a 6-item self-report scale that was designed to assess resilience as the ability to bounce back from stress. It has proved adequate reliability, shown adequate internal consistency (*α* ranging from 0.80 to 0.90) and test–retest reliability (*r* = 0.62–0.69) and validity.

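### Parental distress is an outcome, an unqualified psychiatric exclusion can be applied differently before and after staff training, and the stated comparison ignores the enrolment scores that would correct part of the imbalance

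*Protocol article*

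**What the plan says.** Under Eligibility criteria {10}, parents are excluded if they "have mental psychiatric problems or under legal supervision, or guardianship of social services". The same sentence gives a functional limit to two neighbouring criteria: the intellectual handicap must hinder learning, and communication must fail despite a translator. The psychiatric term has no such limit.

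Objectives {7} seeks superiority "in infants’ clinical outcomes, parental mental health and professional’s self-care and satisfaction". Outcomes {12} lists parental stress, anxiety and depression as secondary outcomes. Questionnaires for parents names the scales; for the depression scale, "The cutoff score of ≥ 13 indicates an elevated risk of depression".

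Intervention description {11a} sets the order of events at sites 1–5 after the control phase: "A 3-month wash-out period will be used for the local training process and assessment of site readiness, while enrolment will be halted". Then, "After that, recruiting will continue, and the experimental intervention will be started". Training and certification includes "psychosocial needs of families (resilience, stress and anxiety, or mourning" in the staff curriculum and aims to reach 90% of NICU staff. The allocation and blinding sections say that start times are not randomised, that concealment does not apply, and that hospitals and professionals are not blinded.

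Statistical methods {20a} compares control with intervention data from sites 1–5 using chi-square tests, analysis of variance, or Mann–Whitney or Kruskal–Wallis tests. The mixed model with covariates in that section is described for weight gain. Table 1 (Participant timeline {13}) schedules parental questionnaires at enrolment and at the short-term and mid-term assessments.

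**The concern.** The exclusion touches the same construct as the outcome. Where a criterion of this kind is open to judgement, how strictly it is applied helps to decide how distressed the enrolled parents are. At sites 1–5 the two groups are enrolled at different times, by staff who know the phase and who are trained on families' psychosocial needs in the interval. Nothing in the article holds the application of the criterion constant across that interval.

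If strictness changes in either direction, the groups differ in distress before any treatment effect, and an unadjusted comparison of questionnaire scores attributes that difference to the intervention. The parental mental-health claim is at stake. The primary growth and implementation outcomes are not shown to be affected.

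**Working it through.** **Plan's own figure.** The article gives no figure on this point. Its only calculated number is 46 per group for weight gain. It reproduces: 2 × (1.960 + 1.645)² × 2.5² / 1.9² = 45 by the normal approximation, and 45.98, hence 46, by the t-test. It does not bear on the parental outcomes.

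**Step 1: can the groups differ at entry?**
- The criterion has no operational limit (Eligibility criteria).
- Control parents enter before staff training and intervention parents after it (Intervention description).
- Start times are not randomised and staff are not blinded (allocation and blinding sections).
- No rule in the article fixes how the criterion is applied across phases.

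A phase difference is therefore possible. Its direction is not fixed. More attention to parental distress could raise exclusions. Training that promotes family involvement could lower them.

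**Step 2: how large could it be?** The cutoff of 13 is in the article. All other inputs are assumed: depression score normal with mean 11 and SD 6, and a fraction e of parents at or above 13 excluded in one phase and none in the other.
- z = (13 − 11)/6 = 0.333, so p = P(score ≥ 13) = 0.369.
- Mean score at or above 13 = 11 + 6 × 0.377/0.369 = 17.13, which is 6.13 above the overall mean.
- Shift in mean = e·p × 6.13/(1 − e·p).
- Remaining proportion at or above 13 = p(1 − e)/(1 − e·p).

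| e | e·p | Shift in mean (points) | Shift in SD | Proportion ≥ 13 |
|---|---|---|---|---|
| 0 | 0 | 0 | 0 | 36.9% |
| 10% | 0.037 | 0.24 | 0.04 | 34.5% |
| 20% | 0.074 | 0.49 | 0.08 | 31.9% |
| 30% | 0.111 | 0.76 | 0.13 | 29.1% |

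If the extra exclusions fall in the intervention phase, its mean is lower by these amounts. If they fall in the control phase, the intervention mean is higher by the same amounts.

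A second illustration needs no mean or SD. Suppose a fraction f of all families is excluded in one phase only.
- If they are the most distressed, the shift is φ(z_f)/(1 − f), where φ is the standard normal density and z_f its upper-f point: 0.05, 0.11 and 0.20 SD for f = 2%, 5% and 10%.
- If they are drawn at random from the most distressed 30%, whose mean is 1.159 SD above average, the shift is 1.159·f/(1 − f): 0.02, 0.06 and 0.13 SD.

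**Step 3: what carries through to the outcome, and what does adjustment do?** Step 2 selects on the outcome score itself, but screening comes before the follow-up questionnaires. With equal SDs and an assumed correlation of 0.5 between distress at entry and at outcome, the shifts halve: 0.24 × 0.5 = 0.12, 0.49 × 0.5 = 0.24 and 0.76 × 0.5 = 0.38 points. If selection acts only through the enrolment score and the relation is linear, the unadjusted bias is slope × difference in mean enrolment score, and adjustment for that score removes it. Residual variance is multiplied by 1 − 0.5² = 0.75, so precision also improves. Selection on distress that the score does not capture remains.

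**Step 4: does the article already adjust?** The adjustment in Statistical methods {20a} belongs to weight gain. The regression models for subgroup analyses {20b} name centre, sex, and gestational age or main diagnosis. Neither names the enrolment questionnaire score.

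**The case against.** A reader might infer that training will make staff exclude more distressed parents, so that intervention scores improve artificially. The documents do not support this. The curriculum covers psychosocial needs, communication and promotion of family involvement; it does not mention recognition, screening or psychiatric assessment. The effect could run the other way. The article also does not name who applies the criterion. It plans antenatal consent where possible, and otherwise an approach soon after birth, which leaves staff little time to observe distress.

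A reader might also infer that any anxiety or depression excludes a parent. That is the literal wording, but the neighbouring terms concern capacity and legal status, and questionnaires at enrolment suggest that symptomatic parents are expected. No passage makes a score an exclusion. Excluding some parents with psychiatric problems restricts the population; it does not formally contradict the objective, and it may have a rationale because certified caregivers perform tasks autonomously. The full protocol may define the term.

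The numerical case rests wholly on assumed inputs. Narrowing the eligibility criterion now could also create the imbalance it is meant to prevent. Enrolment began in February 2023 and the latest assigned start is month 12, so if the schedule held, control enrolment had ended at every site before publication in April 2024.

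These points remove any claim about direction or size and rule out a mid-trial change of threshold. They leave standing an open-ended criterion related to the outcome, applied in two non-randomised phases, and a stated comparison that does not use the baseline scores already collected.

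**Conclusion.** The concern holds as a risk of phase-dependent selection of unknown direction and size, confined to secondary parental psychological outcomes at sites 1–5. The documents establish the unqualified wording, the phase structure, the lack of blinding and the unadjusted comparison. They do not establish that exclusions will differ by phase. The shifts of 0.2 to 0.8 points (0.04 to 0.13 SD) assume mean 11, SD 6 and one-sided exclusion of 10% to 30% of parents at or above 13. They shrink if entry and outcome scores correlate imperfectly, and they change sign if the exclusions fall in the other phase.

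The analysis should be changed, because the correction uses data already scheduled and also gains precision.

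**What to change.** 1. For each parental psychological outcome that has an enrolment measurement, replace the unadjusted tests with a regression or mixed model adjusted for the enrolment score and for site.
2. Report enrolment scores by phase at sites 1–5.
3. State that the psychiatric exclusion is applied identically in both phases and that an enrolment questionnaire score is not in itself a reason for exclusion. Date this clarification, and leave the eligibility threshold unchanged for the rest of the trial.

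The cost is a few lines of analysis text and one table; no new data are needed. Adjustment corrects only measured differences among enrolled parents. It says nothing about excluded parents, for whom only a screening record with reasons by site and phase would help. Outcomes without an enrolment measurement gain nothing from it and should be interpreted with that in mind.
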